### Endpoints

The primary endpoint is OS, defined as the time from randomization to death from any cause or lost to follow-up. Secondary endpoints include the 1-year and 3-year OS rates, PFS, intracranial metastasis rate, and neurocognitive function changes assessed by MMSE at specified intervals. Progression-free survival (PFS) will be assessed by investigators according to the Response Evaluation Criteria in Solid Tumors (RECIST) version 1.1 criteria, without blinded independent central review. Validated patient-reported outcome measures will be used to assess QoL where feasible. Exploratory analyses will aim to identify specific patient subgroups that derive the benefit from PCI based on clinical characteristics and longitudinal dynamic biomarkers.

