### Sample size and statistical power

The sample size calculation is based on the primary endpoint of OS, using a non-inferiority design. Assuming an exponential survival distribution, simulation based on available data indicates that the median OS in the PCI group is approximately 22 months. Considering that MRI-based surveillance may reduce treatment-related toxicities associated with PCI, the median OS in the MRI surveillance group is estimated to be approximately 23.5 months [5, 8, 20]. Based on a non-inferiority margin corresponding to a hazard ratio (HR) of 1.25, with a one-sided alpha of 0.025 and a power of 80%, a total of 387 OS events are required. With an estimated enrollment period of 60 months and an additional follow-up period of 20 months, a total of 544 patients (272 per arm) needs to be enrolled, accounting for a 5% dropout rate. The calculation was performed using PASS 2021 software.

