The advent of immunotherapy has further reshaped the treatment landscape of LS-SCLC, with durvalumab consolidation following chemoradiotherapy now established as the new standard of care. The ADRIATIC trial results indicated that while durvalumab was effective whether or not patients undergo PCI, those receiving PCI showed slightly higher 3-year OS rate: 62.1% in the PCI group compared to 50.2% in the non-PCI group (HR 0.75). Grade 3–4 adverse events occurred in 28.4% of the PCI group versus 19.8% in the non-PCI group(19,28). These findings necessitate a reassessment of the utility of PCI within current immunotherapy treatment landscapes. Our randomized study includes patients who have received first-line immunotherapy, particularly those receiving consolidation immunotherapy, aiming to reassess the role of PCI in the modern treatment era and identify patients who may derive benefit from prophylactic irradiation.

Although our trial has been carefully designed, several limitations should be acknowledged. First, this is an open-label study, as blinding of treatment assignment is not feasible given the inherent characteristics of radiotherapy. Second, the choice of local treatment after the detection of brain metastases in the surveillance arm (e.g., WBRT vs. SRS) was decided jointly by patients and investigators, which may introduce heterogeneity in subsequent patient management and clinical outcomes. To minimize its impact, all post-progression treatments will be systematically documented, and prespecified subgroup analyses will be performed. Third, although MMSE was selected because of its simplicity, feasibility, and widespread use in routine clinical practice and previous PCI-related studies, it may have limited sensitivity for detecting subtle cognitive impairment associated with PCI, particularly in executive function, attention, and delayed recall. More sensitive assessment tools such as the Montreal Cognitive Assessment (MoCA), may provide a more detailed evaluation of PCI-related neurotoxicity and should be incorporated into future prospective studies. Finally, the prolonged follow-up required for overall survival assessment may increase the risk of patient attrition. To mitigate this, we will implement centralized data management and active patient engagement strategies to ensure data integrity and follow-up compliance.

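### The primary OS definition makes loss to follow-up an endpoint event alongside death, which contradicts the sample size and can shift the non-inferiority result

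*Protocol article*

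**What the plan says.** The protocol article defines the primary endpoint once, under Endpoints: "The primary endpoint is OS, defined as the time from randomization to death from any cause or lost to follow-up". Loss to follow-up is joined to death by an 'or', with nothing to mark it as a censoring time.

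Other sections bear on the point without correcting it:

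- **Sample size and statistical power** sizes the trial on deaths. It assumes exponential survival, and states that "the median OS in the PCI group is approximately 22 months" and that "the median OS in the MRI surveillance group is estimated to be approximately 23.5 months". It uses a "non-inferiority margin corresponding to a hazard ratio (HR) of 1.25", one-sided alpha 0.025 and 80% power, and concludes that "a total of 387 OS events are required". Enrolment of 544 is then described as "accounting for a 5% dropout rate".
- **Statistical analysis** names Kaplan-Meier, the log-rank test and Cox models for OS, and gives no censoring rule.
- **Overall study design** says patients are followed for survival until death, consent withdrawal or study closure.
- **Discussion** lists as a limitation that "the prolonged follow-up required for overall survival assessment may increase the risk of patient attrition".

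**The concern.** OS is time to death from any cause, and a patient who goes missing is normally censored when last known alive. An analyst coding the primary endpoint literally from this sentence would score every such patient as having had the event. Three things follow.

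1. The hazard ratio tested against 1.25 becomes that of a composite of death and loss. Loss at a similar rate in both arms pulls it toward 1. When MRI surveillance is truly worse by the margin, this makes a false claim of non-inferiority easier.
2. If loss differs by arm, the hazard ratio is biased directly, in either direction. The trial is open-label and one arm receives an extra treatment, so equal retention cannot be taken for granted.
3. The 387-event target would be reached partly with patients not known to have died.

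The secondary 1-year and 3-year OS rates, if read on the same definition, inherit the problem: a patient lost alive at month 10 would count as dead at one year.

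**Working it through.** **Inputs from the protocol article.** PCI median 22 months, MRI median 23.5 months, exponential survival, margin HR 1.25, one-sided alpha 0.025, 80% power, 387 events, 60 months' enrolment plus 20 months' follow-up, 5% dropout, 544 patients allocated 1:1.

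**Inputs assumed here.** Uniform accrual, exponential loss independent of death, and the split of loss between arms.

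**Step 1: reproduce the plan's figures.**

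- Assumed true HR = 22/23.5 = 0.936.
- Events = 4(1.960 + 0.842)² / [ln(1.25/0.936)]² = 4 × 7.849 / 0.2891² ≈ 376 (Schoenfeld). The Freedman form gives 381. Both are within 3% of 387.
- Power at 387 events = Φ(√387/2 × 0.2891 − 1.960) = 81.2%.
- Death hazards are ln2/22 = 0.03151 and ln2/23.5 = 0.02950 per month. The probability of death by month 80 is 1 − (e^(−20λ) − e^(−80λ))/(60λ), which gives 0.761 and 0.740, mean 0.7505.
- N = 387/0.7505 = 515.7, and 515.7/0.95 = 542.8, against 544 stated.

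The division by 0.95 matters here. It treats dropouts as patients who yield no event, which conflicts with the endpoint definition.

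**Step 2: how many events would not be deaths.** With 5% of 544 (27.2 patients) lost and the plan's medians, about 392.3 deaths are expected by month 80. The share of losses is 27.2/(392.3 + 27.2) = 6.5%, or about 25 of 387 events.

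**Step 3: effect on the test.** Let λ be the death hazard and g the loss hazard. If loss counts as an event, the composite HR is (λ_MRI + g_MRI)/(λ_PCI + g_PCI). The probability of declaring non-inferiority at 387 events is Φ(√387/2 × ln(1.25/composite HR) − 1.960). Each g is solved so that the stated percentage is lost before death or month 80.

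Worked example, true HR 1.25, 7.5% lost on PCI and 2.5% on MRI: g = 0.00330 and 0.00122. Composite HR = (0.03938 + 0.00122)/(0.03151 + 0.00330) = 1.166. Probability = Φ(9.836 × ln(1.25/1.166) − 1.960) ≈ 0.10.

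True HR 1.25, where the correct type I error is 2.5%:

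| Loss, PCI / MRI | Composite HR | Type I error |
|---|---|---|
| 5% / 5% | 1.244 | 2.8% |
| equal loss hazard, 5% overall | 1.233 | 3.4% |
| 6% / 4% | 1.212 | 4.9% |
| 7.5% / 2.5% | 1.166 | 10% |
| 10% / 2% | 1.121 | 19% |
| 4% / 6% | 1.276 | 1.5% |

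True HR 0.936, where the correct power is 81.2%:

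| Loss, PCI / MRI | Composite HR | Power |
|---|---|---|
| 5% / 5% | 0.938 | 80.7% |
| 4% / 6% | 0.964 | 73% |
| 2.5% / 7.5% | 1.003 | 58% |
| 2% / 10% | 1.045 | 42% |

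If all 544 patients are followed to month 80 rather than stopping at 387 events, the 10%/2% error becomes about 21% and the 2%/10% power about 45%. A simulation of 3,000 trials with full follow-up gave about 21% and 47%.

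**Step 4: after the correction.** Counting deaths only, 387 events give 81.2% power at HR 0.936 and 2.5% type I error at HR 1.25. Neither 387 nor 544 changes.

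**The case against.** The best defence is that the sentence describes when observed OS time ends and that the authors meant losses to be censored. The rest of the article fits that reading: the sample size treats dropouts as non-events, Kaplan-Meier and Cox methods are built to censor, and the Discussion treats attrition as a risk to be reduced. A journal article also condenses its protocol. The benign reading is plausible, so it is not established that lost patients will in fact be analysed as deaths. It does not repair the text, though. Condensing leaves detail out, whereas this sentence adds an event type to the primary endpoint. Nor is it a complete list of when observation ends, because it omits study closure and withdrawal of consent.

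The second objection is size, and part of it stands. At the only loss rate the protocol gives, 5% overall, and with balanced loss, the distortion is small: 2.8–3.4% type I error and a loss of about one percentage point of power at most. The large figures need unequal loss, for which the protocol gives neither amount nor direction, and an imbalance toward MRI makes the test conservative at the margin.

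Third, these calculations assume loss unrelated to prognosis. If loss is informative and differs by arm, censoring would be biased too, so the correction does not remove every effect of attrition.

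**Conclusion.** The concern holds. The primary endpoint is wrong as written and contradicts the trial's own sample size calculation, whatever the authors intended. If applied literally, about 25 of 387 events would not be known deaths at 5% loss. The effect on type I error is slight with balanced loss, roughly doubles the nominal level at 6% versus 4%, and reaches about 19% at 10% versus 2%. The opposite imbalances cut power to 73% and 42%. These figures rest on exponential survival and on exponential loss independent of death, and the arm-specific rates are assumptions. Because this sentence defines the primary endpoint of a phase III non-inferiority trial, it must be corrected before the analysis.

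**What to change.** Reword the endpoint definition so that OS is time from randomization to death from any cause, with patients not known to have died, including those lost to follow-up, censored at the date last known alive. State that only deaths count toward the 387 events, that the 1-year and 3-year OS rates use the same definition, and carry the same wording into the SAP. An analysis scoring losses as events may be kept as a labelled sensitivity analysis, if at all. Reporting loss to follow-up by arm would let readers judge whether it could be informative.

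The cost is one sentence in the endpoint definition and its counterpart in the SAP. The event target, the 544 patients and the trial's duration are unaffected. Because the sentence concerns an endpoint, the change would go through the IRB and registry update that the protocol already provides for.

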### Sample size and statistical power

The sample size calculation is based on the primary endpoint of OS, using a non-inferiority design. Assuming an exponential survival distribution, simulation based on available data indicates that the median OS in the PCI group is approximately 22 months. Considering that MRI-based surveillance may reduce treatment-related toxicities associated with PCI, the median OS in the MRI surveillance group is estimated to be approximately 23.5 months [5, 8, 20]. Based on a non-inferiority margin corresponding to a hazard ratio (HR) of 1.25, with a one-sided alpha of 0.025 and a power of 80%, a total of 387 OS events are required. With an estimated enrollment period of 60 months and an additional follow-up period of 20 months, a total of 544 patients (272 per arm) needs to be enrolled, accounting for a 5% dropout rate. The calculation was performed using PASS 2021 software.

### Data collection and management

All data, including demographic characteristics, disease history, treatment details, imaging results, laboratory tests, adverse events, and patient-reported outcomes, will be prospectively collected via electronic case report forms (eCRFs). Serious adverse events (SAEs) will be reported to the principal investigator and the respective Institutional Review Board (IRB) within 24 h of awareness. To ensure data quality, range checks and logic checks will be built into the eCRF system. Data entry and management will be performed by trained clinical research coordinators under the supervision of the principal investigator. Source data verification will be performed periodically. Participant confidentiality will be maintained, and all stored data will be de-identified.

### Statistical analysis

The OS and PFS will be analyzed using the Kaplan-Meier method, with differences compared using the log-rank test. Hazard ratios (HRs) and corresponding 95% confidence intervals (CIs) will be estimated using Cox proportional hazards models. The cumulative incidence of brain metastasis will be compared using Gray’s test, considering death as a competing risk. Neurocognitive function scores will be analyzed using mixed-effects models for repeated measures to assess changes from baseline over time. Subgroup analyses for OS will be performed using Cox proportional hazards models. All statistical tests will be one-sided for non-inferiority, with a significance level of 0.025. Statistical analyses will be performed using IBM SPSS Statistics (version 29.0) or R software (version 4.2.0).

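### The rule that every test is a one-sided non-inferiority test fits only overall survival, and even there the decision is not tied to the 1.25 margin

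*Protocol article*

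**What the plan says.** The Sample size and statistical power section of the protocol article sets up one non-inferiority comparison: "The sample size calculation is based on the primary endpoint of OS, using a non-inferiority design". It gives a margin of 1.25 on the hazard ratio, a one-sided alpha of 0.025, 80% power and 387 deaths. No margin is given for any other endpoint.

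The Statistical analysis section then names the methods. For the two time-to-event endpoints: "The OS and PFS will be analyzed using the Kaplan-Meier method, with differences compared using the log-rank test". Hazard ratios with 95% confidence intervals come from Cox models. For the brain: "The cumulative incidence of brain metastasis will be compared using" Gray's test, with death as a competing risk. MMSE scores go into mixed-effects models for repeated measures, and the subgroup analyses are Cox models for OS. One sentence on testing covers all of these: "All statistical tests will be one-sided for non-inferiority, with a significance level of 0.025". The figure 1.25 does not appear in this section.

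Two other sections state what some of these analyses are for. Neurocognitive function assessment aims to evaluate possible neurotoxicity of PCI relative to surveillance. The Endpoints section says: "Exploratory analyses will aim to identify specific patient subgroups that derive the benefit from PCI".

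**The concern.** A non-inferiority test needs a margin. Without one there is no null hypothesis and no p-value. The blanket rule imposes such a test on endpoints that have no margin, in a section that has just named tests of equality for two of them. An analyst cannot follow both instructions.

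The rule also points the wrong way for some of the questions asked. Showing that surveillance is not worse than PCI on the MMSE by more than some amount does not show that PCI causes decline. Showing that surveillance is non-inferior within a subgroup does not show that another subgroup gains from PCI.

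For OS, the trial is sized for a comparison with 1.25, but the only test named by type compares with 1. These tests have different critical values and very different power. If sidedness, direction and margins are settled only when the data are in, in an open-label trial, the choice will be open to the charge that it followed the results.

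**Working it through.** **Inputs, all from Sample size and statistical power except the 1:1 allocation (Study design and setting).** Median OS 22 months with PCI and 23.5 months with surveillance, exponential; margin 1.25; one-sided alpha 0.025; power 80%; 387 deaths; accrual 60 months plus 20 months of follow-up; 5% dropout; 544 patients.

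**Step 1: reproduce the plan's figures.** The implied hazard ratio, surveillance against PCI, is 22/23.5 = 0.936. For 1:1 allocation (Schoenfeld),

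events = 4 × (1.960 + 0.842)² / [ln(1.25/HR)]².

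- HR 0.936 unrounded: 376 events (381 by Freedman's formula), within 3% of 387.
- HR rounded to 0.94: 386.5, so 387, the stated figure.
- Patients, assuming uniform accrual: mean probability of death 0.7505; 387/0.7505 = 515.7; 515.7/0.95 = 543, or 544 with equal arms.

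The design is therefore a real test against 1.25.

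**Step 2: compare the two possible OS tests at 387 deaths.** The standard error of the log hazard ratio is 2/√387 = 0.1017.

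| | Test against 1.25 | Log-rank test, null HR = 1 |
|---|---|---|
| Largest observed HR that succeeds | 1.25 × exp(−1.96 × 0.1017) = 1.024 | exp(−1.96 × 0.1017) = 0.819 |
| Power at HR 0.936 | Φ(ln(1.25/0.936)/0.1017 − 1.96) = 81.2% | Φ(−ln(0.936)/0.1017 − 1.96) = 9.5% |
| Power at HR 0.94 | 80.1% | not needed |

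For the log-rank test, success means significance in favour of surveillance. The test against 1.25 has a type I error of 2.5% at a true hazard ratio of 1.25, as intended.

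**Step 3: apply the blanket rule to each analysis.**

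| Analysis | Margin given? | Named method | Can the stated rule be applied? |
|---|---|---|---|
| OS | 1.25 | Log-rank; Cox HR with 95% CI | Yes, through the Cox interval, but the link is not stated |
| PFS | None | Log-rank for differences; Cox HR with 95% CI | No |
| Brain metastasis | None | Gray's test of equality | No |
| MMSE | None | Mixed-effects model | No; it would also miss the neurotoxicity question |
| OS subgroups | 1.25 carries over | Cox model | Yes, but it answers another question |

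On the last row: within a subgroup, rejecting the null shows that the hazard ratio is below 1.25. Failing to reject may only reflect few deaths. Neither outcome shows that PCI helps there, or that its effect differs between subgroups. That needs a treatment-by-subgroup interaction.

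**The case against.** The strongest reply concerns OS. The margin, the alpha and the direction are fixed in the sample-size section. The Cox interval is planned, and comparing the upper limit of a two-sided 95% interval with 1.25 is the one-sided 0.025 test. What is absent is one linking sentence, which a journal article may leave to a full protocol or analysis plan that is not shown. This stands. A reader might infer that the plan cannot test its margin correctly; the article does not support that.

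A reader might also infer that a non-significant log-rank result will be taken as non-inferiority. With 387 deaths and a true hazard ratio of 1.25, a two-sided 5% log-rank test is non-significant 41% of the time, so that rule would err in 41% of trials instead of 2.5%. But the article states no such rule, and its sentence on one-sided non-inferiority testing speaks against it. The 41% measures a hypothetical misuse, not this plan.

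Two further limits stand. The test is undefined for three groups of analyses, not four, because the subgroup analyses are for OS and inherit its margin. The consequence is also modest: the secondary endpoints do not decide the trial, the PFS hazard ratio and its interval remain interpretable, and a one-sided 0.025 test has the same critical value in its own direction as a two-sided 0.05 test. The search for patients who benefit is exploratory and, according to Dynamic peripheral blood monitoring, uses machine learning models, so the testing rule bears on it only in part.

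What the reply does not remove is the word all. That is a rule stated wrongly, not a detail left out. An analysis plan could repair it only by contradicting the article.

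**Conclusion.** The point holds, and it should be fixed before analysis. The blanket rule is undefined for PFS, brain metastasis and MMSE, and conflicts with the tests of difference named for the first two. It does not address the neurotoxicity question for MMSE, and it cannot identify who benefits from PCI in the OS subgroups.

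For OS the weakness is narrower: the correct interval is planned but not tied to 1.25, and the one test named has about 9.5% power to favour surveillance at the design hazard ratio, against about 80% for the test that the trial was sized for. Those figures assume 387 deaths, 1:1 allocation, proportional hazards and the usual large-sample variance of the log hazard ratio. They show that the two tests are not interchangeable. They do not show that the trial is underpowered or its primary analysis invalid.

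**What to change.** Replace the blanket sentence with two statements.

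1. For OS only: non-inferiority is tested one-sided at 0.025 and concluded if the upper limit of the two-sided 95% confidence interval for the Cox hazard ratio, MRI surveillance against PCI, is below 1.25. The log-rank test is supportive.
2. PFS, brain metastasis, MMSE and treatment-by-subgroup interactions are analysed with two-sided tests of difference at 0.05 and reported with 95% confidence intervals. Subgroup findings remain exploratory.

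The 387 deaths and 544 patients are unchanged, and no data collection changes. The cost is two sentences, carried into the analysis plan. Study design and setting says that significant changes to statistical analyses go to the IRB and, as required, the trial registry, so the correction should follow that route before any comparative data are examined.

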## Discussion

The role of PCI in LS-SCLC has been established for decades, primarily based on a meta-analysis of trials conducted prior to the advent of high-precision MRI for staging and follow-up [5]. With technological advancements facilitating the early detection and treatment of brain metastases, PCI applicability in the contemporary era is increasingly questioned. This study, a randomized phase III trial comparing PCI with MRI surveillance in LS-SCLC patients who achieve CR/PR after first-line therapy, is designed to address this critical gap in evidence and provide further insights into which populations may derive greater benefit from PCI.

A meta-analysis in 1999 established the role of PCI in SCLC, demonstrating a 5.4% improvement in the 3-year survival rate and a significant reduction in the incidence of brain metastases (58.6% without PCI vs. 33.3% with PCI, *p* < 0.001) among patients after first-line chemoradiotherapy [5]. However, the trials included in this meta-analysis predate the routine use of MRI and were restricted to LS-SCLC patients achieving CR. With the widespread use of modern MRI, recent retrospective studies indicate that PCI continues to reduce the incidence of brain metastases in LS-SCLC patients with CR or PR, but this reduction does not translate into a survival benefit and may compromise quality of life [6, 21, 22]. Growing evidence suggests that PCI is frequently associated with varying degrees of neurocognitive decline, the severity of which is comparable to the neurotoxicity observed following WBRT for overt metastases [5, 8]. Consequently, approximately 40% of eligible patients decline PCI due to concerns regarding neurotoxicity [23, 24]. To provide more definitive evidence, our trial design incorporates longitudinal neurocognitive assessments at multiple time points to delineate the short- and long-term neurocognitive sequelae of PCI and their associations with survival outcomes. Furthermore, given prospective evidence that hippocampal avoidance may preserve the topological organization of brain networks [24, 25], we recommend the use of HA-PCI in this study, investigating whether HA-PCI can mitigate PCI-related neurocognitive toxicity and potentially improve survival outcomes in patients with LS-SCLC.

The value of PCI in the MRI era was first questioned in ES-SCLC. A landmark randomized trial from Japan in ES-SCLC demonstrated that active MRI surveillance without upfront PCI resulted in non-inferior OS compared to PCI [8]. This pivotal finding prompted a revision of international guidelines, which now favor MRI surveillance over PCI for ES-SCLC. The lack of survival benefit in this population is likely attributable to the competing risk of death; patients with ES-SCLC face an excessively high risk of systemic progression and mortality, meaning the intracranial control provided by PCI often lacks sufficient time to translate into an extension of overall survival. Now, the role of PCI in the modern treatment era of LS-SCLC is also being challenged. While PCI reduces brain metastasis rates, its ability to improve survival warrants prospective validation. Prior studies demonstrated that among LS-SCLC patients who did not receive PCI, a substantial proportion presented with a limited number of intracranial lesions at the time of first brain metastasis, thereby offering greater opportunities for treatment with SRS [12, 14]. This feasibility facilitates a novel therapeutic strategy: early identification via active MRI surveillance followed by the timely SRS treatment.

A recent prospective study demonstrated that for patients with SCLC presenting with limited brain metastases and no prior brain irradiation (including PCI), SRS/SRT reduced neurological mortality (11.0% vs. 17.5% at 1 year) compared to historical WBRT controls [14]. Consequently, active MRI surveillance combined with timely SRS/SRT has demonstrated significant value in the management of SCLC, and better preserved neurocognitive function [10–13, 12]. Furthermore, under close MRI-based surveillance, most patients who develop intracranial recurrence after initial SRS present with a limited number of new lesions that are detected early, thereby allowing for continued salvage treatment with SRS/SRT rather than WBRT. To further explore this strategy, our trial will characterize the patterns and burden of brain metastases and subsequent salvage therapies, and evaluate its potential clinical value.

The advent of immunotherapy has further reshaped the treatment landscape of LS-SCLC, with durvalumab consolidation following chemoradiotherapy now established as the new standard of care. The ADRIATIC trial results indicated that while durvalumab was effective whether or not patients undergo PCI, those receiving PCI showed slightly higher 3-year OS rate: 62.1% in the PCI group compared to 50.2% in the non-PCI group (HR 0.75). Grade 3–4 adverse events occurred in 28.4% of the PCI group versus 19.8% in the non-PCI group(19,28). These findings necessitate a reassessment of the utility of PCI within current immunotherapy treatment landscapes. Our randomized study includes patients who have received first-line immunotherapy, particularly those receiving consolidation immunotherapy, aiming to reassess the role of PCI in the modern treatment era and identify patients who may derive benefit from prophylactic irradiation.

Although our trial has been carefully designed, several limitations should be acknowledged. First, this is an open-label study, as blinding of treatment assignment is not feasible given the inherent characteristics of radiotherapy. Second, the choice of local treatment after the detection of brain metastases in the surveillance arm (e.g., WBRT vs. SRS) was decided jointly by patients and investigators, which may introduce heterogeneity in subsequent patient management and clinical outcomes. To minimize its impact, all post-progression treatments will be systematically documented, and prespecified subgroup analyses will be performed. Third, although MMSE was selected because of its simplicity, feasibility, and widespread use in routine clinical practice and previous PCI-related studies, it may have limited sensitivity for detecting subtle cognitive impairment associated with PCI, particularly in executive function, attention, and delayed recall. More sensitive assessment tools such as the Montreal Cognitive Assessment (MoCA), may provide a more detailed evaluation of PCI-related neurotoxicity and should be incorporated into future prospective studies. Finally, the prolonged follow-up required for overall survival assessment may increase the risk of patient attrition. To mitigate this, we will implement centralized data management and active patient engagement strategies to ensure data integrity and follow-up compliance.

Despite these limitations, this trial is designed to address an important clinical question in LS-SCLC. If the MRI surveillance strategy is demonstrated to be non-inferior to PCI, it may represent a more personalized and function-preserving approach for LS-SCLC survivors. In particular, by reassessing the role of PCI in the modern era of immunotherapy, this study may provide clinically relevant insights that align with the evolving treatment landscape of LS-SCLC. The results will provide evidence on whether active MRI surveillance can reduce exposure to the long-term neurotoxic effects of PCI without compromising survival outcomes. Furthermore, exploratory analyses will aim to characterize patient subgroups who may derive greater benefit from PCI, potentially providing insights into more individualized patient selection. In conclusion, this study seeks to clarify the clinical utility of PCI in the modern treatment era and contribute to the optimization of evidence-based strategies for managing brain relapse risk in LS-SCLC [26].

